### Data analysis

Factorial design mixed-effects models will be applied to compare questionnaire battery scores between experimental groups and the control across measurements. In addition, we will perform an interrupted time series analysis to estimate the effects of different types of interventions on longitudinal ecological momentary assessment outcomes.

In the statistical analysis, we will incorporate data from participants who have completed a minimum of 21 Ecological Momentary Assessment (EMA) entries, spread over the one-month period dedicated to evaluating the intervention. For the assessment of the intervention’s enduring effects, the analysis will consider participants who have logged at least three EMA entries during the follow-up phase. In addition, within the intervention group, we will include those who have accessed the app and engaged with the self-guided intervention modules on a minimum of four occasions and at least once, respectively; this will represent the minimal therapeutic exposure required for the study. For the analysis of secondary outcomes, we will include participants who have completed the initial baseline assessment as well as at least one subsequent follow-up assessment.

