### Study design

The study was pre-registered within the Open Science Framework (OSF) repository: https://osf.io/z4xqd.

A two-arm participant-blinded randomized control trial will be conducted via a mobile app. The study will compare an intervention experimental condition with a waitlist control condition.

Throughout the duration of the study, participants assigned to the experimental group will have access to self-guided psychological interventions.

Participants will be asked to complete daily EMA questions, as well as questionnaire battery assessments at multiple timepoints: 1) at baseline – in the first week, following onboarding questionnaire; 2) after one month; 3) after two months; 4) after three months.

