### Sample size calculation

A simulation-based power analysis was performed to determine the sample size, premised on the use of a linear mixed-effects model with subject-level random intercepts and a small effect size of the intervention. This effect size assumption was informed by literature on the efficacy of mobile interventions in mitigating addictive behaviors (for a review, see 25). The simulation indicated that a minimum of 360 participants would be necessary to achieve an 80% power threshold for detecting a significant group effect. The sampling strategy has been devised to capture maximal demographic variance within the sample, with particular attention to characteristics such as gender, age, geographic location, and socioeconomic status.

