### Procedure

The study will be conducted with the use of *Nałogometr 2.0*, a mobile app designed to reduce craving and lapse risk in SUD and enhance post-treatment effects (available freely on Google Play and App Store). Prior to the first login, participants will be automatically navigated through all the necessary permissions and consents regarding data collection. Following the app installation, participants will be prompted with an onboarding questionnaire to collect demographic data. They will have a one-week window to complete the initial standardized questionnaire battery assessment. The responses from this initial assessment will serve as the baseline for subsequent evaluations throughout the study. The schedule of these assessments is outlined in **Figure 1**.

During a three-month period, participants will be required to engage in daily EMA assessments and to complete a monthly questionnaire battery. Concurrently, physiological data will be continuously gathered via smartbands.

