## Results

### Hypotheses

The primary outcomes of this study are centered on the hypothesis that participants receiving the intervention, as opposed to those in the control condition, will exhibit reduced levels of craving and fewer lapses at the one-month follow-up post-app implementation relative to their baseline levels. It is anticipated that this downward trend in craving and lapse incidents will be sustained throughout subsequent evaluations. Additionally, it is conjectured that a single session of self-guided psychological intervention may yield a notable decrement in both craving intensity and the risk of a lapse occurring. Furthermore, the hypothesis extends to posit that participants in the intervention condition will demonstrate lower levels of substance addiction, reduced symptoms of anxiety and depression, and an elevated sense of life satisfaction when compared to those in the control group, as measured by the relevant standardized questionnaires.

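### The questionnaire model names no adjustment for each scale's own baseline score, so the best-supported reading is an unadjusted change from baseline: unbiased, but less precise than the collected data allow

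*Protocol article*

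**What the plan says.** The Data analysis section gives the model for the questionnaires: "Factorial design mixed-effects models will be applied to compare questionnaire battery scores between experimental groups and the control across measurements". No covariate, factor level or target contrast is named.

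The Study design section schedules "questionnaire battery assessments at multiple timepoints: 1) at baseline", then "in the first week, following onboarding questionnaire; 2) after one month; 3) after two months; 4) after three months". That is four waves with baseline first, and Table 1 has a baseline column for every scale. The Procedure section says of the first battery: "The responses from this initial assessment will serve as the baseline for subsequent evaluations throughout the study". For the secondary outcomes, Data analysis states that "we will include participants who have completed the initial baseline assessment as well as at least one subsequent follow-up assessment".

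The Hypotheses section expects lower dependence, anxiety and depression and higher life satisfaction in the intervention arm, "as measured by the relevant standardized questionnaires". The Sample size calculation is "premised on the use of a linear mixed-effects model with subject-level random intercepts and a small effect size of the intervention" and refers to a group effect, but does not mention the questionnaires.

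**The concern.** Each participant's own baseline score is usually the strongest available predictor of the later score on the same scale. Here it is collected from everyone who enters the secondary analysis, so using it costs no participants. The stated model is a factorial over measurements with no baseline adjustment named. If baseline is one of its levels and the arms are free to differ there, the arm-by-time contrast subtracts the whole baseline score, where adjustment would subtract only the part that predicts follow-up. The extra noise widens the confidence interval.

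The Discussion prepares for small effects and a high dropout rate, so precision is scarce. The hypotheses on dependence severity, anxiety and depression, and life satisfaction all rest on this model. At stake is efficiency on secondary outcomes. The change contrast itself is not biased.

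**Working it through.** **The plan's own figure.** The sample size statement reads: "The simulation indicated that a minimum of 360 participants would be necessary to achieve an 80% power threshold for detecting a significant group effect". It can be neither reproduced nor refuted, because the effect size, alpha, correlation and number of measurements are not given. For orientation, at two-sided 0.05 and 80% power a single measurement needs 786 participants in total for d = 0.2 and 350 for d = 0.3. With d = 0.2 and four averaged measurements, 360 follows if rho is about 0.28. The figure is attainable, but it says nothing about questionnaire power.

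**Inputs.** From the article: four waves (Study design), baseline required (Data analysis), a random-intercept model (Sample size calculation). Assumed: 1:1 arms, unit variance, compound symmetry with correlation rho, a constant effect at months 1 to 3, complete waves, two-sided 0.05.

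**Variances (per participant).**
- One month, change from baseline: 2(1 − rho). Baseline-adjusted: 1 − rho².
- Mean of months 1 to 3, change: (1 + 2rho)/3 + 1 − 2rho. Adjusted: (1 + 2rho)/3 − rho².
- In both cases the difference is 1 − 2rho + rho² = (1 − rho)², which is positive for every rho below 1.

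**Power at one month.** Give the change contrast 80% power, that is, a noncentrality of 1.960 + 0.842 = 2.802. Adjustment multiplies this by √(change variance / adjusted variance), and power is Φ(noncentrality − 1.960).

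| rho | change variance | adjusted variance | √ratio | noncentrality | power adjusted |
|---|---|---|---|---|---|
| 0.3 | 1.40 | 0.91 | 1.240 | 3.48 | 94% |
| 0.5 | 1.00 | 0.75 | 1.155 | 3.24 | 90% |
| 0.7 | 0.60 | 0.51 | 1.085 | 3.04 | 86% |
| 0.8 | 0.40 | 0.36 | 1.054 | 2.95 | 84% |

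For the mean of months 1 to 3 the same steps give 98%, 94%, 89% and 86%.

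**Absolute check.** With d = 0.2 and 360/2 = 180 per arm, the mean-of-follow-up contrast has these powers (change, then adjusted): 50% and 81% at rho 0.3; 64% and 84% at 0.5; 85% and 93% at 0.7; 96% and 98% at 0.8. A simulation of 10,000 trials agreed (65% and 84% at rho 0.5; 85% and 92% at 0.7), and both contrasts averaged 0.20, so neither is biased. With d = 0.3 the gap is 84% and 99% at rho 0.3, 94% and 99% at 0.5, and 99% and 100% at 0.7, so it can be negligible.

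**Months 1 to 3 only, no covariate.** The variance is (1 + 2rho)/3, against (1 + 2rho)/3 − rho² adjusted. Starting from 80% unadjusted, adjustment gives about 87% at rho 0.3, 94% at 0.5 and over 99% at 0.7. Dropping the baseline wave without using the score does not avoid the loss.

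**Main effect over all four waves.** Randomisation makes the expected baseline difference zero, so this effect is (0 + d + d + d)/4 = 0.75d. It matters only if that main effect is the test.

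**The case against.** The strongest objection is that the article does not say baseline is an outcome level, nor does it exclude a covariate. The Procedure wording, and the Measures statement that batteries are given at one, two and three months, would both fit follow-up outcomes with baseline as covariate. The entry rule fits either model. A condensed article may leave covariates and contrasts to a fuller document. A four-wave model with a common baseline mean would be nearly as efficient as adjustment, and the text does not rule it out.

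Much of this stands: the four-wave unadjusted reading is an inference. It is nonetheless the best-supported one, because a model is stated, baseline is listed as its first measurement, and no adjustment or constraint is named. Only an unstated covariate or constraint would avoid the loss.

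A reader might infer that the arm effect is diluted by a quarter. The documents do not support that. The group effect appears in the sample size paragraph, which is not tied to the questionnaires, and the usual test in such a factorial is arm-by-time, which is not diluted. A reader might also infer a material loss of power on every secondary outcome. The direction holds for any rho below 1, but the size depends on values the article does not give.

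**Conclusion.** The point holds as an efficiency issue on the secondary questionnaire outcomes. As best read, the stated model tests an unadjusted change from baseline, which is unbiased but less precise than the data allow. A one-month contrast with 80% power would gain roughly 4 points (rho 0.8) to 14 points (rho 0.3) from adjustment, and the mean of months 1 to 3 would gain 6 to 18 points over the same range. This rests on compound symmetry, 1:1 arms, complete waves and, for the mean, a constant effect. The 80% starting point is an assumption, since the article claims no power for the questionnaires. No rho is given, so the gain on a particular scale is not established and is small where rho is high. Shrinkage to three quarters of a constant follow-up effect would arise only if an arm main effect including the baseline wave were the test, which the article does not state for these outcomes.

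**What to change.** In Data analysis, replace the sentence on questionnaire scores with one of two models:
- month 1, 2 and 3 scores as outcomes, with arm, month, arm-by-month, and the same scale's baseline score and its interaction with month; or
- all four waves as outcomes, with a common baseline mean across arms.

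Report the adjusted arm difference at each month and averaged over months 1 to 3. Do not test a group main effect that includes the baseline wave.

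Add a limitation: the baseline battery may be completed up to a week after the intervention arm's modules open (Randomization and Procedure), so some baseline scores may already reflect the intervention and attenuate the adjusted estimate. The unadjusted change is attenuated more, because it subtracts the whole of any early effect and adjustment only a fraction. Do not respond with an analysis restricted to baselines entered before module use. Controls have no module access during the study, so that restriction could exclude only intervention participants and would break the randomised comparison.

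The cost is wording alone. No data, participants or assessments are added, and baseline is already required for entry.

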Although interest in mobile health (mHealth) technologies is surging, with over 300,000 applications available in digital marketplaces (38), only a limited number have undergone clinical evaluation before being released for widespread usage (39). Despite many of these applications employing scientific terminology to substantiate their benefits, the evidence supporting them is frequently of poor quality or altogether absent (40). Nonetheless, those apps that have been subject to scientific scrutiny have demonstrated promising outcomes, with positive effects on health-related behaviors (41). The inherent characteristics of mHealth interventions render them an encouraging support mechanism for patients with Substance use disorder (SUD) — given their remote delivery, they can be utilized on demand, providing immediate assistance and support amid episodes of increased craving. Consequently, mHealth solutions are particularly valuable for relapse prevention among patients who have concluded formal treatment. The persistent and considerable risk of relapse following treatment poses a significant challenge in the management of addictive disorders, and mHealth interventions offer a viable approach due to their convenience, ease of use, and broad accessibility. Moreover, mHealth solutions hold the potential to overcome barriers to accessing therapy, such as social stigma, while remaining cost-effective and widely available.

There are some mobile apps dedicated to reducing substance use already available on the market (e.g. *Quitzilla, Drinker’s Helper, Helpic*), but only a few of them have been scientifically tested – examples of such apps include *Drink Less* (42) for alcohol use or *Assess, Plan, Track, Tips (APTT;*
43
*)* and *Norwegian Cannabis Cessation app* (44) for cannabis use. Their features include tracking day-to-day substance usage in a form of sobriety calendars, as well as psychoeducational content on substance dependence and psychological components on recognizing and dealing with triggers and craving.

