Given these insights, it becomes imperative to provide patients with addictive disorders access to scientifically validated, evidence-based mobile health (mHealth) solutions. This paper introduces a protocol for a two-arm randomized controlled trial (RCT) designed to evaluate the effectiveness of self-guided, mobile-delivered CBT- and mindfulness-based psychological interventions. The goal is to enhance the post-therapy effects of SUD treatment and aid in the prevention of lapses. These interventions will be administered through the Nałogometr 2.0 app, a science-based mHealth application developed to decrease craving intensity and the risk of lapses in individuals experiencing problematic substance use or those diagnosed with SUD.

The Nałogometr 2.0 app incorporates multiple self-guided psychological interventions predominantly rooted in cognitive behavioral therapy and mindfulness. It offers users the autonomy to interact with any module at their convenience without adhering to a predetermined regimen, thereby affording greater flexibility in tailoring psychological interventions to meet their current needs. Beyond delivering psychological intervention modules, the app is also engineered to foster self-monitoring and self-management by enabling users to self-record their behaviors, and mental and physiological states through Ecological Momentary Assessment (EMA). Additionally, users receive personalized feedback in response to their input.

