### Randomization

Upon their initial login to the mobile application, participants in each group (alcohol, cross-addiction, and cannabis), will be randomly allocated to either the experimental or control condition based on a code they receive during recruitment. Codes corresponding to experimental and control conditions were generated seperately for each group and then put in a randomized sequence. The randomization was done via an online randomization tool (45. [Online] Available from: https://www.sealedenvelope.com/simple-randomiser/v1/lists). Block sizes were determined using the simulation tool (45. [Online] Available from: https://www.sealedenvelope.com/randomisation/simulation/, taking into account planned sample sizes. Participants assigned to the experimental condition will gain immediate access to all psychological interventions following their initial app login. Those in the control condition will have access only to the daily EMA questions and the sobriety calendar, a tool for tracking their substance use. They will be provided access to the complete version of the app, including the psychological interventions, subsequent to the study’s conclusion - which is scheduled for 98 days after the first login.

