Participants assigned to the intervention group will be granted immediate access to all intervention modules upon logging into the app using their unique code. They will have the autonomy to interact with any of the interventions at their discretion without any mandatory commitment. Adherence to a stringent schedule for engaging with the interventions is not a prerequisite for participants in the intervention condition.

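### The planned interrupted time series is said to estimate effects of different intervention types, but modules open together and are self-chosen by current need, so the design does not identify by-type effects

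*Protocol article*

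**What the plan says.** The Data analysis section names two methods. Mixed-effects models are for the questionnaire scores. For the EMA data the article states that "we will perform an interrupted time series analysis to estimate the effects of different types of interventions on longitudinal ecological momentary assessment outcomes". EMA records craving and lapses (Measures), and these are the primary outcomes.

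How types come into use is described elsewhere:

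- Timing of access (Randomization): "Participants assigned to the experimental condition will gain immediate access to all psychological interventions following their initial app login".
- Choice (Mobile application content): "They will have the autonomy to interact with any of the interventions at their discretion without any mandatory commitment".
- Schedule (same section): "Adherence to a stringent schedule for engaging with the interventions is not a prerequisite for participants in the intervention condition".
- Purpose of the free choice (Introduction): "affording greater flexibility in tailoring psychological interventions to meet their current needs". Of mobile interventions in general, the Introduction says that "they can be utilized on demand, providing immediate assistance and support amid episodes of increased craving".
- What is randomised (Randomization): participants "will be randomly allocated to either the experimental or control condition based on a code they receive during recruitment". Module type is not randomised.

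No run-in without modules is stated. The baseline questionnaire battery itself falls in the first week, when modules are already open. The exploratory analyses listed in the Discussion concern engagement, psychological domains and physiological measures. By-type effects are not among them, so nothing marks this analysis as exploratory.

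**The concern.** An interrupted time series takes its causal force from an interruption whose timing has nothing to do with the current level of the outcome, set against a usable stretch of data before it. Here the interruption for a given type is the moment when a participant chooses it, and the article's own account ties that moment to current need. A type picked in bad moments will tend to be followed by improvement, and a type picked in good moments by worsening, even if neither does anything.

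Nothing in the design separates the types: no assigned order, no staggered release, no randomisation of type. The control arm does not help, because its members have no modules to choose from and so supply no counterpart to the users of a particular type.

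At stake is a published statement that one kind of module lowers craving or lapses and another does not, when the contrast may show only the state in which each is opened.

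**Working it through.** **The plan's own figure.** The article gives no number for by-type effects. Its minimum of 360 participants at 80% power is for the arm effect and cannot be checked, since the numerical effect size, alpha, intraclass correlation and number of measurements are not given. It is reachable: with d = 0.2, two-sided alpha 0.05 and 28 daily measures, 180 per arm requires an intraclass correlation of about 0.44. It does not bear on this point.

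**Simulation inputs (assumptions unless a source is given).**

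- 180 experimental participants, half of the 360 in the Sample size calculation.
- 28 daily EMA entries, about the one-month evaluation period.
- Craving = person level + daily state. The state has SD 1 and day-to-day correlation 0.6.
- Three module types, all with true effect zero. Baseline log-odds of use is -2, so each is used on about 1/(1 + e^2) = 12% of days.
- Type 1 is chosen more at high craving, type 2 regardless of craving, type 3 more at low craving. The log-odds slope is 0, 0.25, 0.5 or 1.0 per SD, that is, odds ratios of 1.00, 1.28, 1.65 and 2.72.
- 300 runs per setting, standard errors clustered by person. The test is type 1 against type 3 at a nominal 5%. Monte Carlo standard error at 5% is sqrt(0.05 × 0.95 / 300) = 1.3 percentage points.

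**Codings.** The article does not say how the interruption is coded, so two were tried: (a) change in craving from the day of a session to the next day; (b) a level step after first use of each type, with person effects and a time trend. A third model regresses next-day craving on use, adjusted for craving at the time of choice.

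| Odds ratio of choice per SD | (a) apparent effect, types 1 / 2 / 3 (SD) | (a) false difference | (b) apparent effect, types 1 / 2 / 3 (SD) | (b) false difference | Adjusted: false difference |
|---|---|---|---|---|---|
| 1.00 | 0.00 / 0.00 / 0.00 | 4% | 0.00 / 0.00 / -0.01 | 6% | 4% |
| 1.28 | -0.10 / 0.00 / +0.10 | 97% | +0.04 / 0.00 / -0.04 | 11% | 5% |
| 1.65 | -0.19 / 0.00 / +0.19 | 100% | +0.07 / 0.00 / -0.08 | 25% | 4% |
| 2.72 | -0.32 / 0.00 / +0.33 | 100% | +0.15 / 0.00 / -0.15 | 79% | 3% |

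**Hand check of (a).** Expected next-day change given state u is (0.6 - 1)u = -0.4u. For a weak logistic slope s, mean state differs between use and non-use days by about s. The apparent effect is then about -0.4 × s: -0.4 × 0.25 = -0.10, as simulated, and -0.4 × 0.5 = -0.20 against -0.19. This is regression to the mean and nothing else.

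**Direction.** Under (a) the type opened at high craving looks helpful. Under (b) the same type looks harmful.

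**Other settings.** With 200 users, 30 days, 85% EMA completion, autocorrelation 0.5 and two null types each used on about 15% of days, log-odds slopes of 0.4 and 0.8 (odds ratios 1.49 and 2.23) gave false differences in 19% and 56% of trials under a level-change model, with gaps of 0.08 and 0.17 SD. At slope 0 the rate was 5%.

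**Does adjustment cure it?** The last column holds only because choice there depends solely on craving measured at the moment of choice. The article states daily EMA and no EMA tied to the start of a session. If choice follows craving half a day after the last entry and the outcome comes half a day later, adjusting for that last entry still leaves a false gap of about 0.15 SD at odds ratio 1.28 (significant in roughly nine trials in ten) and 0.30 SD at 1.65 (essentially all trials).

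**The case against.** The strongest reply is that this is one sentence in a condensed article. The statistical analysis plan and the pre-registration are not shown, and covariates, lags, the pre-use window and multiplicity are usually settled there. EMA records many of the states likely to drive choice (mood, stress, anxiety, loneliness, fatigue and others), and the adjusted model above restores the nominal error rate when measured craving is all that drives choice. That stands in part. A reader might infer that by-type effects cannot be recovered by any analysis, and the article does not support that. The accurate statement is that the design does not identify them. Recovery needs the untestable assumption that no unmeasured state drives choice, and a daily entry need not capture the state at the start of a session.

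A reader might also infer that a false ranking of modules will appear. That goes too far. The article states neither a ranking, nor a between-type contrast, nor a by-type hypothesis, and it gives neither the pattern nor the strength of choice. The simulated pairing, one type favoured at high craving and another at low, is unfavourable. With choice unrelated to state there is no excess error.

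Two further inferences should be resisted. Counting every topic and module named under Mobile application content as a separate type, and computing a family-wise error from that count, has no basis: the article does not define types or say how they would be tested. Nor can one say how many users would lack data before first use of a type, because no usage rate is given.

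**Conclusion.** The point holds in a limited form. The article states a causal aim by type on EMA outcomes that include the primary ones, and its own description of access and choice removes what an interrupted time series needs to deliver it. By-type estimates can reflect selection and regression to the mean.

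Under assumed choice strengths of 1.28 to 2.72 per SD and no true effect, the false-difference rate was 11% to 79% for a level change at first use and 97% to 100% for session coding, with opposite signs. Those figures show what can happen under the stated assumptions and do not predict this trial's results.

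The randomised comparison of arms does not depend on which module is chosen and is unaffected.

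**What to change.** In the Data analysis section, replace the claim to estimate effects of different intervention types. State instead that the time series describes within-person associations between use of module types and EMA outcomes, that these results are exploratory and hypothesis-generating, and that no causal ranking of types will be drawn.

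Add that the model adjusts for the EMA state (craving, mood, stress and the other recorded states) last recorded before each module use, and that unmeasured state at the moment of choice remains a limitation.

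The cost is one reworded sentence with a short addition, slightly more analysis work, and the loss of a by-type causal claim that the design does not support. No change to the app or to data collection is needed.

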**Method:**

This study is designed to assess the effectiveness of mobile interventions in mitigating cravings and preventing lapses among individuals diagnosed with SUD. Employing a two-armed, randomized controlled trial framework, the study will evaluate a self-administered psychological intervention delivered through a mobile application, Nałogometr 2.0. Over a period of three months, participants will engage with intervention modules that primarily incorporate mindfulness techniques and Cognitive Behavioral Therapy (CBT) principles. Ecological Momentary Assessment (EMA) will be utilized to gather longitudinal data on a range of variables that are indicative of craving intensity and the risk of lapse. In addition to this, a monthly-administered battery of questionnaires will be employed to gauge the severity of substance dependence, as well as to measure levels of anxiety, depression, and overall life satisfaction.

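### The later-period EMA analysis can show an effect sustained under continued module access but not persistence after access ends, and its entry and exposure filters select on post-randomisation behaviour

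*Protocol article*

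**What the plan says.** Data analysis in the Protocol article sets two participation rules for the EMA outcomes. The main analysis takes participants with at least 21 entries, "spread over the one-month period dedicated to evaluating the intervention". A later analysis is then described: for the intervention's "enduring effects, the analysis will consider participants who have logged at least three EMA entries during the follow-up phase". A further rule, for the intervention arm only, requires at least four occasions of app access and at least one use of a module. It follows both entry rules in the text and is not tied to either, so I read it as applying to both analyses.

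On access, Study design states: "Throughout the duration of the study, participants assigned to the experimental group will have access to self-guided psychological interventions". The Abstract agrees: "Over a period of three months, participants will engage with intervention modules". Randomization adds: "Participants assigned to the experimental condition will gain immediate access to all psychological interventions following their initial app login". Mobile application content says of the same participants: "They will have the autonomy to interact with any of the interventions at their discretion without any mandatory commitment". Controls have the EMA questions and sobriety calendar, and receive the modules after the study concludes, "which is scheduled for 98 days after the first login".

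Hypotheses places the primary comparison at one month and continues: "It is anticipated that this downward trend in craving and lapse incidents will be sustained throughout subsequent evaluations".

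**The concern.** An enduring effect, assessed in a follow-up phase set apart from the period in which the intervention is evaluated, is easily read as benefit that outlasts treatment. On the described schedule, the intervention arm can still use every module on every day of that phase. A difference between arms could then exist only because participants are still using the modules. For a service deciding whether to offer the app for a limited time or indefinitely, these are different conclusions, and the trial can inform only one of them.

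The second issue is who is analysed. Logging entries and opening modules happen after allocation and may depend on it, and on how the participant is doing. The Discussion expects that dropout may be high. People who lapse and stop logging would leave the later analysis, and the exposure rule removes low users from one arm with no matching removal from the other. The groups compared are then no longer those that randomisation formed.

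**Working it through.** No figure in the plan bears directly on this point, and the sample size of 360 is not affected by it. The check sets the passages side by side, with simple arithmetic on the timeline.

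**1. Access by arm and period**

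| Period | Intervention arm | Control arm |
|---|---|---|
| Month 1 | all modules, on demand | no modules |
| Rest of the study, to day 98 | all modules, on demand | no modules |
| After day 98 | no withdrawal described | modules released |

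Sources: Abstract, Study design, Randomization and Mobile application content.

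**2. Days after the evaluation month**

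The study ends 98 days after first login. The length of the month is not given in days, so I take 28 to 31.

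- 98 − 28 = 70 days, and 70/98 = 71%.
- 98 − 31 = 67 days, and 67/98 = 68%.

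On all of these 67 to 70 days the intervention arm has full access. Controlled days without access: 0.

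**3. Could the follow-up phase lie elsewhere?**

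Data analysis does not date it. Months 2 and 3 are inferred from the one-month evaluation window, the three months of daily EMA under Procedure and the one-month primary hypothesis. The other candidate is after day 98. The article describes no data collection then, and controls would have the modules, so there would be no untreated comparator. Neither placement yields a controlled off-access period.

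**4. What the three-entry rule permits**

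This assumes that the phase is months 2 and 3 and that there is one EMA entry per day. The phase lasts about 61 days if it is taken as two calendar months, and up to 70 days from step 2.

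- Later phase: 3/61 = 4.9% and 3/70 = 4.3% of days.
- Month 1, taken as 30 days: 21/30 = 70%.

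These are minimum requirements for inclusion, not expected amounts of data. The article does not say whether the 21-entry rule also applies to the later analysis.

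**5. The exposure rule**

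A participant with 21 entries has very probably opened the app on four occasions already, so in the main analysis the part that binds is likely to be the single module use. If the later analysis requires only three entries, the four-occasion part can bind too. In both cases the rule is applied in one arm only, because controls have no modules to open.

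**The case against.** The strongest reply is that the article does not use follow-up to mean time after treatment. Hypotheses counts the one-month follow-up from the start of app use, and the Discussion speaks of monthly follow-up assessments across the three months. On that usage a follow-up phase with continuing access is no contradiction. Enduring can then mean what Hypotheses calls sustained, which is a real question if novelty or use fades, and one that the arms can address because controls have no modules until day 98. This stands. Apart from the filters, the later contrast is a proper randomised comparison of access with no access.

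Three stronger readings are tempting, and the documents do not support them.

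- A reader might infer that the intervention is said to last one month in one place and three months in another. The one-month span in Data analysis is a window for evaluation, not a statement of the intervention's length, so there is no such conflict.
- A reader might infer that the plan claims benefit after access is withdrawn. No section says so; the wording only leaves room for it.
- A reader might take 4% to 5% as the data the later phase will yield. It is a floor that rests on an assumed window, and EMA is daily with daily reminders.

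It is also fair that Figure 1, which gives the assessment schedule, is not shown, and that a fuller protocol or analysis plan may date the phase. Dating it would remove the ambiguity, but on the schedule described it would not create an off-access comparison. Nor does any of this answer the selection caused by the entry and exposure rules.

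**Conclusion.** The point holds as one of estimand and analysis set. As described, the later EMA analysis estimates whether an effect is sustained while access continues; it cannot show persistence after access ends, because there are 0 days of controlled off-access comparison. That result does not depend on whether the phase is months 2 and 3 or falls after day 98. The figures of 67 to 70 days and 4% to 5% do depend on the months 2 and 3 reading.

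The entry minimum and the one-arm exposure rule add selection on post-randomisation behaviour. Its size cannot be worked out from the documents, which give no retention or module-use figures by arm. Restricting one arm to those who used the modules would tend to favour the intervention if users are also the better-motivated participants, but that is a presumption.

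No number in the plan is shown to be wrong. The change is worth making because it limits what may be concluded about craving and lapses, the primary outcomes, beyond month 1.

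**What to change.** 1. Under Data analysis, give the start and end of the follow-up phase in days from first login.
2. Restate the estimand of the later analysis as the effect of continued module access versus no access in that phase, and state that persistence after access ends is not assessed. The term enduring can then be replaced by sustained, in line with Hypotheses.
3. For each primary outcome, estimate arm differences by month in one mixed model (a generalised one for lapses), using all available EMA entries from all randomised participants in the arm to which they were allocated. Report by arm how many participants contribute no entries in each month, since the model relies on assumptions about the missing entries.
4. Keep the 21-entry, three-entry and minimum-exposure thresholds for a sensitivity analysis only, labelled as such.
5. Report module use in the later phase beside the estimate. Engagement metrics already plans to track completed interventions within specific timeframes.

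This needs rewording and one restated model per outcome, with no new data and no change to what participants receive. The price is giving up any claim of persistence, and an estimate that may be smaller because participants with little or no use are included.
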